## 2. Materials and Methods

### 2.1. Study Design

This study will be a two-arm, noninferiority randomized controlled trial (RCT) comparing blended CBT intervention for PPD (Blended Be a Mom) to the usual treatment that women receive to treat PPD in primary healthcare centers (treatment as usual; TAU). Participants in both the Blended Be a Mom and TAU conditions will complete baseline, postintervention, and follow-up (three and six months postintervention) assessments through a link sent by email that gives access to the survey.

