### 2.4. Recruitment and Eligibility Assessment

Participants will be recruited in primary healthcare units of the region in routine care appointments during the postpartum period. Alternative recruitment methods (e.g., other institutions, online advertisement) will be considered if sample recruitment difficulties arise (e.g., if the sample size is not achieved, or if the current COVID-19 pandemic disrupts the contact with patients within healthcare institutions). Local healthcare providers (e.g., primary care nurses) will be informed about the study and will ask women if they are interested in participating. Women will be informed in detail about the study, both verbally and through a written flyer. If they are willing to participate, they will be asked to sign an informed consent form and to complete a questionnaire including sociodemographic information, a questionnaire to screen for the presence of depressive symptoms (Edinburgh Postnatal Depression Scale), and other eligibility criteria questions (e.g., technology access, not currently undergoing treatment for PPD). Assessment of depressive symptoms will be conducted every two weeks during the period of the study. When women have a positive screen (indicating the presence of clinically relevant depressive symptoms) and meet the remaining eligibility criteria, they will be further contacted by the researchers through telephone or email to inform them that they will proceed to the second phase of the study. In the second phase, an interview (SCID-5) will be conducted by the researcher (licensed psychologist) to assess the presence of the diagnosis of PPD. Women with a clinical diagnosis of PPD will be eligible to participate in the study and will be included in the third phase of the study. In the third phase of the study, eligible women will receive an email containing a link to complete an online self-report questionnaire (baseline assessment). The flowchart of the study is presented in Figure 1, demonstrating the recruitment and eligibility assessment.

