### 2.5. Randomization

After completing the baseline assessment, participants will be randomly assigned (blocked randomization, allocation 1:1) to the intervention (Blended Be a Mom) or the TAU conditions (see Figure 1). Randomization will be conducted by a researcher blind to the assessment procedure and will be performed using a computerized random number generator. Women in both conditions will be informed about their assigned treatment condition. Blinding for treatment conditions will not be possible.

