#### 2.7.2. Primary Outcome

Changes in depressive symptoms, the primary outcome, will be measured with the Portuguese version of the Edinburgh Postnatal Depression Scale (EPDS) [40].The EPDS is a 10-item scale (e.g., “I have felt sad or miserable”) that assesses how women felt over the last seven days concerning several symptoms using an individualized four-point Likert scale (from 0 to 3). The total score can range between 0 and 30, and higher scores are indicative of more severe depressive symptoms. In Portuguese validation studies, a score of 10 or higher suggests the presence of clinically relevant depressive symptoms. The Portuguese version of EPDS showed good levels of internal consistency (Cronbach’s alpha = 0.85) and adequate validity [40].

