### 2.8. Sample Size and Statistical Analyses

The sample size for this study was determined based on power analysis (G*Power). A sample of 45 women per condition is required to detect medium effects in comparison analyses, considering the primary outcome. Considering an expected dropout rate of 20%, we plan to recruit a sample of at least 110 participants (55 per condition) to account for attrition effects.

Statistical analyses to examine the efficacy of the program will be conducted following the intention-to-treat (ITT) and per-protocol (PP) principles in accordance with the CONSORT recommendations [53]. ITT analyses allow us to examine data from all randomized participants, even those with missing values on outcome measures. In contrast, PP analysis includes only participants who followed the assigned treatment protocol. Statistical analyses will be performed using the Statistical Package for the Social Sciences (SPSS, Version 25.0; IBM SPSS) and the Mplus program (Version 7). Linear mixed models will be conducted to determine the effects of the intervention over time (time × group interaction effects) on primary and secondary outcomes and changes in psychological competences. Other appropriate statistical analyses such as two-wave latent change score models, reliable change index, Chi-square tests, and within-group effect sizes will be performed, as well as mediator and moderator analysis. Preliminary cost-effectiveness analysis will be conducted from a healthcare cost perspective and a societal perspective, comparing the differences between the intervention and control group on the outcomes, with the differences in the costs generated. The contribution of a health economics expert will be required.

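### As written, the time × group interaction compares raw EPDS changes; adjusting for baseline, or constraining baseline means to be equal, is asymptotically at least as precise and uses data already collected.

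*Protocol article*

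**What the plan says.** Protocol article, section 2.8, names the estimator: "Linear mixed models will be conducted to determine the effects of the intervention over time (time × group interaction effects", applied to the primary outcome, the secondary outcomes and the psychological competences.

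Section 2.7.2 frames the primary outcome as change: "Changes in depressive symptoms, the primary outcome, will be measured with the Portuguese version of the Edinburgh Postnatal Depression Scale". Under section 2.1, women in both arms "will complete baseline, postintervention, and follow-up (three and six months postintervention) assessments", and Table 1 lists depressive symptoms at T0, T1, T2 and T3. T0 is therefore naturally one of the levels of time.

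Section 2.5 puts allocation after the baseline questionnaire: "After completing the baseline assessment, participants will be randomly assigned (blocked randomization, allocation 1:1". On size, section 2.8 states "A sample of 45 women per condition is required to detect medium effects in comparison analyses, considering the primary outcome", with 55 per condition to be recruited to allow for 20% dropout.

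The article mentions neither a baseline EPDS covariate nor a constraint on the T0 group means. It gives no EPDS SD, no correlation between visits and no covariance structure.

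**The concern.** Because T0 precedes allocation, any difference between the arms at T0 is chance. A model that gives each arm its own T0 mean, and measures the effect as departure from it, spends information on estimating a difference known to be zero in expectation. In a saturated model with complete data, the T0-to-T1 interaction term equals the difference in mean raw change and carries the full noise of the baseline measurement. Using T0 as a covariate, or forcing the arms to share one T0 mean, removes only the part of the baseline that predicts follow-up.

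This is a noninferiority trial, so the conclusion rests on a confidence limit, and about 45 women per arm are expected to be analysed. Precision available from data already collected is worth having. Chance imbalance in T0 EPDS is also handled better. A change score does respond to imbalance, but it over-corrects when the slope of follow-up on baseline is below 1.

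**Working it through.** **The plan's own figure.** The only stated figure is 45 per condition. Alpha, power, sidedness, test and numeric effect size are not given, so it cannot be reproduced from the article's inputs. If medium means d = 0.5, a two-sided 5% t-test with 80% power needs 64 per arm, and 45 per arm gives 65% power; d = 0.6 gives 45. None of this affects the present point. The article states no precision figure to reproduce.

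**Inputs.** From the article: visits T0 to T3, T0 before randomisation, 1:1 allocation, 45 analysed per arm, 20% dropout. Assumed, because the article is silent: ρ from 0.3 to 0.7, and the SDs s0 (baseline) and s1 (follow-up).

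**Step 1: one follow-up visit, complete data.** Per woman, up to a common factor:
- raw change: s0² + s1² − 2ρ·s0·s1
- baseline-adjusted: s1²(1 − ρ²)
- difference: (s0 − ρ·s1)², which is never negative

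This is why the change contrast is asymptotically never the more precise. Estimating the slope costs one degree of freedom, which is trivial with about 90 women.

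**Step 2: equal SDs.** The variances become 2(1 − ρ) and 1 − ρ², with ratio (1 + ρ)/2, so the reduction is (1 − ρ)/2. On the SE or CI scale it is 1 − √((1 + ρ)/2). Generalised least squares on the saturated four-visit model, with a free versus a common T0 mean, gives the same variance figures.

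**Step 3: 20% dropout before T1.** In the mixed model, women who drop out still contribute T0. With dropout fraction d, the variances are proportional to (1 − ρ²)/(1 − d) + (1 − ρ)² with free T0 means and (1 − ρ²)/(1 − d) with a common mean. At ρ = 0.5 the reduction is 0.25/(0.9375 + 0.25) = 21%.

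**Step 4: narrower baseline spread.** With s0 = 0.7·s1, the reduction is 1 − (1 − ρ²)/(1.49 − 1.4ρ). At ρ = 0.3 this is 1 − 0.91/1.07 = 15%; at ρ = 0.7 it is 1 − 0.51/0.51 = 0.

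| Reduction from baseline adjustment | ρ = 0.3 | ρ = 0.5 | ρ = 0.7 |
|---|---|---|---|
| Variance, equal SDs, complete data | 35% | 25% | 15% |
| SE or CI width, same assumptions | 19% | 13% | 8% |
| Variance, equal SDs, 20% dropout before T1 | 30% | 21% | 12% |
| Variance, s0 = 0.7·s1, complete data | 15% | 5% | 0% |

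**Step 5: the entry screen.** Section 2.4 requires a positive EPDS screen before the diagnostic interview, and section 2.7.2 says "a score of 10 or higher suggests the presence of clinically relevant depressive symptoms". Selection lowers ρ but also shrinks s0. The table below assumes normal scores and unselected ρ of 0.3, 0.5 and 0.7, and gives ranges over the position of the cut-off (−0.6 to +0.6 SD).

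| Variance reduction after selection | ρ = 0.3 | ρ = 0.5 | ρ = 0.7 |
|---|---|---|---|
| Selection on T0 itself | 12–22% | 8–15% | 4–8% |
| Separate screen, reliability assumed 0.8 | 25–29% | 21–22% | 17–19% |

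The second row is closer to the article, where T0 is a later online questionnaire. Against 35%, 25% and 15% without selection, the screen mostly reduces the gain; only at ρ = 0.7 with a separate screen does it rise slightly.

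**Step 6: what it could mean for the decision (illustration only).** With 45 per arm and equal SDs, the 95% CI half-width is 1.99·√(2v/45) in SD units. At ρ = 0.5, v = 1 for change and 0.75 adjusted, giving 0.42 and 0.36 SD. If the margin were 0.5 SD at one-sided 2.5% (an assumption; the article states no margin), power would go from 51% to 69% at ρ = 0.3, 65% to 77% at ρ = 0.5 and 86% to 91% at ρ = 0.7. With s0 = 0.7·s1 and ρ = 0.3 it would go from 62% to 69%.

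**The case against.** The strongest reply is that the article does not fully fix the model. One sentence in a condensed article leaves open whether T0 means are free, common or adjusted for. A four-visit model with equal T0 means is itself a time × group model, so the sentence is compatible with the remedy. The latent change score models listed in section 2.8 can also carry a path from baseline to change. An analysis plan not shown may settle all this. That stands, and it limits the weight of the point. It does not remove it: the stated effect, the framing of the outcome as change and the visit schedule together lead most directly to the free-baseline contrast.

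Three stronger readings are tempting, and the article supports none of them.

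- A reader might infer that the trial will lose 15% to 35% of its precision. That range is on the variance scale and is simply ρ from 0.7 down to 0.3 with equal SDs, one follow-up contrast and no dropout. The article supplies none of these values.
- A reader might infer that requiring "When women have a positive screen (indicating the presence of clinically relevant depressive symptoms) and meet the remaining eligibility criteria" makes the change contrast worse by lowering ρ. That overlooks the narrower baseline SD, which pulls the other way and mostly wins.
- A reader might infer that the interaction ignores baseline imbalance or biases the result. It subtracts the baseline, imperfectly, and is unbiased under randomisation.

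**Conclusion.** The point holds as an efficiency improvement to a stated method. Read at face value, section 2.8 estimates a difference in raw EPDS change, and using the baseline as randomisation allows is asymptotically at least as precise.

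The size is uncertain because the article gives neither ρ nor SDs. Over ρ from 0.3 to 0.7, the variance gain is 35% down to 15% in the equal-SD, complete-data case, and close to nothing if the T0 spread is much narrower than at follow-up. It vanishes when s0 = ρ·s1. The power figures describe an assumed 0.5 SD margin and are not properties of this trial. No result would be invalid if the model stayed as it is. The change is worth making because it is free and cannot materially hurt a small noninferiority trial.

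**What to change.** State the primary model in one of two forms:

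1. A mixed model on EPDS at T1 to T3, with T0 EPDS and its interaction with time as covariates, plus group, time and group × time.
2. The four-visit time × group model with group means constrained equal at T0: omit the group main effect and include group terms only at post-baseline visits.

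Use an unstructured covariance in either. Report the adjusted group contrast at T1, with its confidence interval, as the primary result. Use the same form for every secondary outcome and psychological competence collected at T0; for those measured only at T0 and T1, the first form reduces to an ordinary analysis of covariance.

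The cost is a sentence in the analysis plan and a change of SPSS syntax. No extra data, visits or participants are needed. If an analysis plan already contains either form, nothing changes beyond saying so. If a gain in precision or power is quoted in support, give the assumed ρ, SDs and margin with it.

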## 3. Discussion

Despite the existence of effective treatment, few women seek professional help to deal with their depressive symptoms in the postpartum period [7,8], indicating the need for a new and innovative format of treatment that can overcome help-seeking barriers. This study aims to evaluate the acceptability and effectiveness of a blended CBT intervention for the treatment of PPD in the Portuguese context by integrating face-to-face sessions with the web-based program Be a Mom.

To our knowledge, this will be the first study to develop a blended CBT treatment protocol for PPD. Blended Be a Mom benefits from both treatment formats, offering the flexibility, accessibility, and self-management of e-health tools as well as clinical support, increased motivation, and higher treatment intensity [21]. Moreover, it can potentially decrease the number of face-to-face sessions and reduce costs in healthcare systems. A blended CBT intervention can therefore increase help-seeking behaviors among women in the postpartum period by providing treatment that mitigates the impact of the identified barriers in professional help-seeking.

Existing studies have revealed that blended treatment for depression can be effective in reducing depressive symptoms and maintaining these gains over a period of six months [28]. Additionally, previous findings have shown that blended interventions are more effective compared to control groups without intervention (i.e., waiting lists) [24] and that it can be as effective as standard CBT treatments [29]. We expect that Blended Be a Mom will be as effective as TAU with regard to long-term effects on primary and secondary outcomes. The feasibility, acceptability, and usability of the blended intervention will be considered in addition to its cost-effectiveness.

Despite its advantages, there is still limited knowledge about the suitability of blended treatment for every patient [20]. Characteristics such as age, severity of symptoms, or the ability to use technology should be considered and further studied to optimize the effectiveness of blended interventions. The results of our study will provide insights into the processes underlying the treatment effects of blended intervention and the characteristics that moderate the effectiveness of blended intervention.

Our study will also be innovative due to the inclusion of daily ecological momentary assessments during the intervention. This approach allows the collection of information in women’s natural environment in real time and therefore prevents retrospective biases [39]. This will provide important information about intraindividual variations over the treatment, the dynamic evolution of PPD symptoms over time, and temporal relationships between mood and other experiences. The inclusion of ecological momentary assessment is recommended in RCTs because it can optimize statistical power effects, improve measurements precision, and potentially increase treatment’s adherence [54]. This data collection method has previously been used both in the postpartum period and in depression disorders, and it was considered feasible and acceptable by the users [55,56].

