This article presents the study protocol for a blended CBT intervention combining face-to-face sessions with the online program Be a Mom for the treatment of PPD in the Portuguese context. In Portugal, the Be a Mom program was developed as a culturally sensitive web-based CBT intervention that is designed as a self-guided tool for the prevention of PPD. Preliminary evidence of Be a Mom’s pilot trial suggests its effectiveness in reducing depressive symptoms among women presenting early-onset PPD symptoms [30], thus supporting its potential as a PPD treatment tool integrated into a blended treatment protocol.

Therefore, we herein outline the protocol for a randomized controlled trial to examine the acceptability and efficacy of a blended CBT intervention for PPD treatment, considering postintervention and follow-up improvements in primary and secondary outcomes. It is expected that the blended CBT intervention will be as effective as treatment usually provided for PPD in decreasing depressive symptoms. In this study, we will evaluate the mediating role of psychological competences (self-compassion, emotion regulation, psychological flexibility) in treatment response. These mechanisms have been core psychological processes underlying the development of the Be a Mom program [31]. Moreover, previous studies have found that these psychological mechanisms were associated with improvements in depressive symptoms in the perinatal period [30,32,33]. We will also examine the moderator effect of characteristics of the patient (e.g., sociodemographic characteristics, motivation for therapy) and of the therapeutic process (e.g., therapeutic relationship, user’s satisfaction) in the efficacy of the blended intervention for PPD.

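### The Discussion expects equal effectiveness on the secondary outcomes too, but the trial is sized on the primary outcome only and the group comparisons it names look for a difference

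*Protocol article*

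**What the plan says.** Section 2.1 describes a "two-arm, noninferiority randomized controlled trial (RCT) comparing blended CBT intervention for PPD" with usual treatment. The Introduction expects the blended intervention to be "as effective as treatment usually provided for PPD in decreasing depressive symptoms". The Discussion states the expectation more widely: "We expect that Blended Be a Mom will be as effective as TAU with regard to long-term effects on primary and secondary outcomes". The Abstract names six secondary outcomes: anxiety symptoms, fatigue, quality of life, marital satisfaction, maternal self-efficacy and mother–child bonding.

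On size, section 2.8 states: "A sample of 45 women per condition is required to detect medium effects in comparison analyses, considering the primary outcome". It then allows for 20% dropout and plans at least 110 women, 55 per condition. On analysis, the same section uses linear mixed models with a time × group interaction "on primary and secondary outcomes and changes in psychological competences". It also lists latent change score models, a reliable change index, chi-square tests and within-group effect sizes. Intention-to-treat and per-protocol analyses are both planned. The section ties none of these methods to a margin or a confidence-limit rule, for the primary or any secondary outcome.

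**The concern.** A statement that one treatment is as effective as another needs evidence that excludes a relevant deficit. A time × group interaction asks whether the arms differ. When it is not significant, the data have failed to show a difference, and they may still be compatible with a sizeable one. The less precise the data, the more easily that result arises.

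For the secondary outcomes, the expectation in the Discussion goes beyond what the sample size was chosen for and beyond what the named comparison can show. If a non-significant interaction were taken as confirmation, the blended format could be described as matching usual treatment on anxiety, bonding and the other outcomes although the trial had not excluded a moderate deficit. Adding a margin and a confidence-limit rule for the EPDS alone would not change this.

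**Working it through.** **Inputs from the document.** 45 women per arm to detect a medium effect on the primary outcome; 20% dropout; 55 per arm recruited (section 2.8); 1:1 allocation (section 2.5). Expected completers: 55 × 0.8 = 44 per arm.

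**Assumptions, not in the document.** Two-sided 5% test; comparison at a single time point; standardised differences; correlation r between baseline and follow-up of 0 to 0.7; a medium effect taken as d = 0.5 or f = 0.25.

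**The plan's own figure.** The article gives no alpha, power or numeric effect, so 45 per arm cannot be reproduced uniquely. A t-test with d = 0.5 and 80% power needs 64 per arm two-sided or 51 one-sided; 45 per arm gives 65% or 76% power. A between-groups repeated-measures ANOVA with f = 0.25, four time points and r = 0.6 needs 90 in total at 80% power, which matches 2 × 45. In either calculation the aim is to detect a difference. For dropout, 90/0.8 = 112.5, so 113 against the planned 110, which is immaterial here.

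**Precision.** The 95% half-width, unadjusted, is t(0.975, 2n − 2) × √(2/n):
- n = 44: 1.988 × √(2/44) = 0.42 SD
- n = 55: 1.982 × √(2/55) = 0.38 SD

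**Chance that a true deficit is non-significant.** Non-central t with noncentrality d × √(n/2) / √(1 − r²). For example, n = 44, d = 0.3, r = 0 gives 0.3 × √22 = 1.41 and a 72% chance. With n = 55, d = 0.3, r = 0.7 it is 0.3 × √27.5 / √0.51 = 2.20 and a 41% chance.

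| n per arm | r | deficit 0.3 SD | deficit 0.4 SD |
|---|---|---|---|
| 44 | 0 | 72% | 54% |
| 44 | 0.5 | 64% | 43% |
| 44 | 0.7 | 51% | 26% |
| 55 | 0 | 66% | 45% |
| 55 | 0.5 | 56% | 33% |
| 55 | 0.7 | 41% | 17% |

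**Several outcomes together.** In a simulation with 44 per arm, no baseline adjustment, all six outcomes truly worse by 0.3 SD and correlated 0.5 (assumed), at least four of the six were non-significant in about 71% of trials and all six in about 35%. So about 65% of such trials would flag at least one outcome.

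**Could margins rescue the wider expectation?** With one-sided 2.5%, 80% power, no true difference and an assumed margin M in SD units, n per arm = 2 × (1.960 + 0.842)² / M². This gives 175 at M = 0.3, 99 at 0.4, 63 at 0.5 and 44 at 0.6. With 45 per arm and no baseline adjustment, power is 30%, 48%, 66% and 81%. Only a wide margin would be workable at the planned size, and that is for one outcome at a time.

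**The case against.** Several points on the other side are sound.

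- **The harm is inferred.** A reader might conclude that the authors plan to treat non-significant results as proof of equal efficacy. The article does not say so. The Discussion sentence is an expectation, not a success criterion or decision rule.
- **The Introduction does not confine the hypothesis.** It states one expectation about depressive symptoms and does not say that this is the only one. The sentence before it sets the aim in terms of primary and secondary outcomes. The two places differ in scope of wording; they do not contradict each other outright.
- **The secondary outcomes are not singled out.** The EPDS gets the same interaction test and the same sizing to detect an effect. The mismatch with the noninferiority label in section 2.1 is the larger problem, and this point should not count it twice.
- **Other analyses are listed, and a mixed model yields an interval.** Its interaction estimate and confidence limits could be read against a margin. That is true, but section 2.8 describes none of the listed methods as a noninferiority or equivalence comparison.
- **Margins and reporting rules may sit in an analysis plan that is not shown.** Their absence is therefore no finding. The point rests on what the article does state: an expectation wider than its sizing, and comparisons that seek a difference.
- **The highest percentages are the unadjusted completer case.** Intention-to-treat analysis uses information from up to 55 per arm, and baseline adjustment or pooling of visits can sharpen the estimate. The range must be given, and its lower end is well below its upper end.

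**Conclusion.** The point holds as a limited one. The Discussion's expectation for the secondary outcomes is not supported by the sizing or by the group comparisons in section 2.8. It is a consequence of the main defect, the noninferiority label set against a difference-type analysis of the EPDS. It needs its own edit because a repair of the EPDS analysis alone would not reach it.

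A non-significant interaction would be weak support for equal effectiveness. A true deficit of 0.3 SD on one outcome would go undetected in about 41–72% of trials, and one of 0.4 SD in about 17–54%. These ranges rest on two-sided 5% tests at one time point, 44 to 55 women per arm and baseline correlations of 0 to 0.7. The document gives neither the test level nor the correlations, and a model over four assessments could be more precise. Even at the favourable end for 0.3 SD, about two trials in five would miss the deficit.

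**What to change.** In the Discussion, limit the expectation of equal effectiveness to the EPDS, or say that the secondary outcomes are exploratory. In section 2.8, add that secondary outcomes are reported as baseline-adjusted between-arm differences with 95% confidence intervals, and that no claim of equal efficacy is drawn from a non-significant interaction. Make both edits together with the repair of the primary noninferiority analysis, so that the scope of the claim is settled once.

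The cost is wording. No extra participants, measurements or visits are needed. The authors give up a claim that the design cannot support.
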